## Abstract

**Background:**

Sedation prior to performance of diagnostic esophagogastroduodenoscopy (EGDE) is widespread and increases patient comfort. But 98% of all serious adverse events during EGDEs are ascribed to sedation. The S3 guideline for sedation procedures in gastrointestinal endoscopy published in 2008 in Germany increases patient safety by standardization. These new regulations increase costs because of the need for more personnel and a prolonged discharge procedure after examinations with sedation. Many patients have difficulties to meet the discharge criteria regulated by the S3 guideline, e.g. the call for a second person to escort them home, to resign from driving and working for the rest of the day, resulting in a refusal of sedation. Therefore, we would like to examine if an acupuncture during elective, diagnostic EGDEs could increase the comfort of patients refusing systemic sedation.

**Methods/Design:**

A single-center, double blinded, placebo controlled superiority trial to compare the success rates of elective, diagnostic EGDEs with real and placebo acupuncture. All patients aged 18 years or older scheduled for elective, diagnostic EGDE who refuse a systemic sedation are eligible. 354 patients will be randomized. The primary endpoint is the rate of successful EGDEs with the randomized technique. Intervention: Real or placebo acupuncture before and during EGDE. Duration of study: Approximately 24 months.

**Discussion:**

Organisation/Responsibility The ACUPEND - Trial will be conducted in accordance with the protocol and in compliance with the moral, ethical, and scientific principles governing clinical research as set out in the Declaration of Helsinki (1989) and Good Clinical Practice (GCP). The Interdisciplinary Endoscopy Center (IEZ) of the University Hospital Heidelberg is responsible for design and conduct of the trial, including randomization and documentation of patients' data. Data management and statistical analysis will be performed by the independent Institute for Medical Biometry and Informatics (IMBI) and the Center of Clinical Trials (KSC) at the Department of General, Visceral and Transplantation Surgery, University of Heidelberg.

**Trial registration:**

The trial is registered at Germanctr.de (DRKS00000164) on December 10^th ^2009. The first patient was randomized on February 2^nd ^2010.

## Background

More than 10 million gastrointestinal (GI) endoscopic procedures are performed every year in the United States only[1,2]. The standard use of systemic sedation to facilitate the performance of esophagogastroduodenoscopy (EGDE) and to increase patient comfort has contributed to the widespread use and acceptance of this procedure. But the perceived benefits of improved patient comfort and satisfaction afforded by parenteral sedation must be measured against the increased risk of adverse cardiopulmonary events and higher attendant costs[3]. Complications that arise from EGDE are usually associated with the use of systemic sedation and the dose given. More than 98% of serious adverse events in upper GI endoscopy like hypotension, aspiration and respiratory depression are ascribed to systemic sedation[4].

Recently, the first S3-guideline for sedation in GI endoscopy in Germany was published to improve patient safety, which demands additional trained personnel and endoscopy equipment[5]. Therefore, it is estimated that sedation and related issues account for up to 40% of total endoscopy costs including overhead and indirect costs[6]. In detail, an additional specialized nurse or physician is required to perform and monitor systemic sedation. Furthermore, systemic sedation impedes the rapid discharge from the hospital, resulting in absence of work of patients concerned.

Acupuncture has been used as a part of Traditional Chinese Medicine (TMC) for more than 2000 years[7]. Many studies have investigated the benefits and success of acupuncture in reducing pain for various acute and chronic diseases. However, most of them had methodological difficulties, e.g. the inclusion of an adequate control group[8]. A Cochrane review from 2009 on acupuncture for migraine prophylaxis reports that even acupuncture at the "wrong" place (sham-acupuncture) could have a significant effect on the primary endpoint[9]. Therefore, the use of a real placebo needle is necessary. With the introduction of a placebo acupuncture needle system some years ago a new and valid instrument to measure placebo effects became available (Figure 1)[10].

**Figure 1 F1:**
[figure not shown]
Image of real and placebo acupuncture needle system

If the use of acupuncture could improve tolerance and examination quality of diagnostic EGDE without sedation it should be possible to increase the willingness of patients to undergo this examination without systemic sedation. Consequently, it would be possible to reduce the rate of serious adverse events due to systemic sedation and to lower the costs for personnel and material.

Up to now, only one double-blind, controlled trial with 90 patients undergoing EGDE was performed in 1978, using real versus sham-acupuncture (1 cm away from the acupuncture point) with 10 needles and electrical stimulation and showing that upper endoscopy was much easier and better tolerated after real acupuncture[11]. But this study misses a clearly defined primary endpoint and a detailed sample size calculation and has the disadvantage of using sham-acupuncture instead of a real placebo acupuncture technique in the control group. An adequately designed randomized double-blinded placebo controlled clinical trial with a well-defined primary endpoint and detailed sample size calculation comparing placebo acupuncture versus real acupuncture to improve success rates in EGDE has not yet been conducted.

## Methods/Design

### Aim of study

The objective of this trial is to compare the rate of successful EGDE (combination of patients' satisfaction and examination quality) in patients receiving pharyngeal anaethesia as well as either real or placebo acupuncture.

### Number of patients needed

The sample size calculation is based on the two-sided chi-square test for difference with respect to the primary endpoint.

A review of the previous literature identified a randomized controlled trial from Abraham et al. with a group of 419 patients comparing the rate of successful EDGE with and without sedation[12]. In both groups a pharyngeal anaesthesia was performed. This trial showed a successful examination rate of 46% in the group without sedation. A successful examination was defined as a composite score of patient satisfaction with the procedure as well as quality of the examination (technical adequacy) as assessed by the endoscopist. These were determined by the administration of standardized Likert scales (patient satisfaction on a scale of 1-5, quality of examination on a scale of 1-4). An EDGE examination was only counted as successful if the patient rated 1 or 2 on the satisfaction scale and the endoscopist rated 4 on the quality of examination scale. Based on the results from this large trial we decided to adapt the definition of successful EDGE for our trial and use the 46% success rate of the non sedated group as baseline for the sample size calculation. We believe that an increase of the success rate by 15% or more to > = 61% in the acupuncture group would be clinically relevant and therefore could impact clinical practice. To detect this difference at a type I error rate of α = 0.05 (two-sided) with power 1-β = 80%, a sample size of n = 173 evaluable patients per group is necessary (SAS 9.1 proc power). The drop out rate within the intervention is expected to be about 2% overall. Therefore, another 8 patients in total have to be randomized to obtain the required number of evaluable patients. The total number of patients needed to be randomized is therefore 354 (Figure 2).

**Figure 2 F2:**
[figure not shown]
Flowchart according to CONSORT

### Eligibility

Inclusion criteria

• Age equal or greater than 18 years

• Patients scheduled for elective diagnostic EGDE without systemic sedation

Exclusion criteria

• Patients classified ASA V

• Participation in another clinical trial which could interfere with the primary endpoint of this study

• Expected lack of compliance

• Impaired mental state or language problems

• Patients with known allergy to lidocaine anaesthetic spray or acupuncture needle material

• Necessity of systemic sedation

• Emergency procedures

• Pregnancy

Subject withdrawal criteria

• At their own request or at request of the legal representative

• If, in the investigator's opinion (physician performing the acupuncture or physician performing the examination), continuation of the trial would be detrimental to the subject's well-being (e.g. strong pain at the insertion points, allergical reactions, other independent acute health problems).

All withdrawn patients will be reported in the final results to guarantee maximum transparency.

### Consent

The ACUPEND- Trial will be conducted in accordance with the protocol and in compliance with the moral, ethical, and scientific principles governing clinical research as set out in the Declaration of Helsinki 1989[13] and Good Clinical Practice http://www.ema.europa.eu/docs/en_GB/document_library/Scientific_guideline/2009/09/WC500002874.pdf. The protocol was approved by the Ethics Committee of the University of Heidelberg (S-273/2009). All patients scheduled for an elective diagnostic EGDE in the Interdisciplinary Center of Endoscopy (IEZ) of the Department of General, Visceral and Transplantation Surgery and the Department of Internal Medicine of the Universitiy of Heidelberg will be screened, informed about the ACUPEND trial and included by physicians of the IEZ supervising in this trial. The study procedure, risks, benefits and data management will be clarified in detail before the patients are asked to give their informed consent.

#### Randomization and procedures for minimizing bias

The study protocol was designed according to the Standards for reporting Interventions in Clinical Trials Acupuncture (STRICTA)[14].

##### Minimizing bias

To achieve comparable groups for known and unknown risk factors, randomization will be performed as a block randomization with alternating block size. Allocation to treatment group will be performed by sealed consecutively numbered envelopes prepared by the Institute of Medical Biometry and Informatics of the University of Heidelberg (IMBI). Randomization will be carried out after the patient has signed the informed consent form and will be documented in the case report file of every patient. The allocation will be controlled by a monitor.

##### Minimizing treatment bias

All physicians who participate in this trial will be trained and updated every 3 month to improve comparable treatment of patients.

Special manuals will be used in the Interdisciplinary Center for Endoscopy (IEZ) to reduce errors. Acupuncture will be performed by physicians of the department of the Interdisciplinary endoscopy center (IEZ) who were trained by experienced acupuncturists with level B diploma and who performed at least 20 acupuncture procedures explained in the intervention chapter under supervision. Furthermore the PS3 device will be used to support the localisation of the correct acupuncture points by measuring loss of skin resistance.

##### Minimizing measurement bias

A study nurse or physician will document and monitor the procedure in the endoscopy and recovery room. Before the endoscopic procedure is performed the acupuncturist will open the allocation envelope. The physician performing the EGDE and the assistant nurse will not be informed about the allocation. Once patients are randomized they will be included into the analysis according to the principle of intention to treat.

#### Study treatment

Patients who are scheduled for EGDE will be screened and informed by a member of the IEZ about the trial before their EGDE procedure. After signing the informed consent form the patients will be prepared by staff nurses for the procedure as usual. A study nurse or physician will be present to monitor and document the procedures (Table 1).

**Table 1 T1:** Study Visit Schedule

	Day of screening and intervention
Past medical history*	X

Informed consent	X

Personal data**	X

Examination of primary endpoints:	X
• Success of EGDE	

Examination of secondary endpoints:	
• Heart rate	X
• Blood pressure	X
• Oxygen saturation	X
• Duration of examination	X
• Willingness to repeat examination under same conditions	X
• Periinterventional complications	X

Safety criteria AE, SAE (2.6)	X

*study-relevant past medical history, past surgical history

** height (cm), weight (kg), gender, smoking customs, chemotherapy, existence of false teeth

All patients will be positioned on a stretcher lying on their backs with 30 degrees reverse Trendelenburg's position. Standard monitoring with SaO_2 _and non-invasive blood pressure will be established. Pharyngeal anaesthesia will be performed with a topical xylocaine spray (AstraZeneca, Germany) in all patients by a nurse or physician.

##### According to the allocation the procedure will be continued

We based the acupuncture point selections on Traditional Chinese Medicine meridian theory to improve tolerance and examination quality of diagnostic EGDE[15].

##### Intervention-group A (placebo acupuncture)

All patients will receive placebo acupuncture at the following points according to the procedure of the Streitberger placebo acupuncture needle system (Figures 1 and 3) [10]:

**Figure 3 F3:**
[figure not shown]
Inserted acupuncture needle

KG 24   Chengjiang   middle line (to reduce choking)[15]

Pericard 6   Neiguan   bilateral   (to reduce gastroenteral motility)[16]

Di 4   Yangxci   bilateral   (to reduce nausea and vomiting)[17]

Half to one inch 32G needles (0.32 × 30 mm stainless steel needle from asia med company, Munich, Germany) will be placed and left in their position for five minutes prior and throughout the endoscopic procedure.

##### Intervention-group B (real acupuncture)

After the described preparation patients will receive a real acupuncture at the following acupuncture points:

KG 24   Chengjiang   middle line   (to reduce choking)[15]

Pericard 6   Neiguan      bilateral      (to reduce gastroenteral motility) [16]

Di 4   Yangxci      bilateral      (to reduce nausea and vomiting)[17]

Half to one inch 32G needles (0.32 × 30 mm stainless steel needle from asia med company, Munich, Germany) will be placed into these points, stimulated for 1-2 seconds to induce de qi sensation and left in this position for five minutes prior and throughout the endoscopic procedure.

To perform EGDE all patients in both groups will be turned on their left side still with a 30 degree reverse Trendelenburg's position.

#### Primary and secondary endpoints

##### Primary endpoint

The primary endpoint will be the rate of successful diagnostic EGDE.

##### Definition of the primary endpoint

Rate of successful elective diagnostic EGDE is defined as a composite score of patient satisfaction with the procedure as well as quality of the examination (technical adequacy) as assessed by the examiner. These were determined by the administration of standardized Likert scales.

##### Assessment of the primary endpoint

Immediately after the elective diagnostic EGDE, the examiner scores the technical adequacy of the examination. Each anatomic area (esophagus, stomach, duodenum up to the second stage, and proximal stomach viewed in retroflexion) that was adequately viewed receives a score of 1 versus 0 if inadequately viewed, for a maximum score (4/4) if all four main anatomic areas of the examination were well visualized. The result will be documented in the CRF with tick boxes by the physician who performed the examination.

The patients are asked to rate their satisfaction with the examination after the completion of EGDE, prior to being told the results of their procedure and prior to discharge from the recovery room, on a Likert scale from 1 = acceptable to 5 = unacceptable. The results will be documented in the CRF with tick boxes by a nurse or physician. An EGDE will be counted as success if patients' satisfaction is 1 or 2 on the Likert scale and the examination quality score is 4/4[12,18-20].

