#### Safety aspects

##### Specification of safety variables

The correct placement of the needles will be checked and if necessary replaced by the physician who performed the acupuncture right before the examination. After endoscopic examination the needles will be checked again. If some of the needles are not in place after examination it will be documented in the CRF.

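### Masking is not protected when patient satisfaction, one of the two components of the primary endpoint, is collected and recorded

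*Protocol article*

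**What the plan says.** All references are to the Protocol article.

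- **Who knows the allocation.** Minimizing measurement bias: "Before the endoscopic procedure is performed the acupuncturist will open the allocation envelope". Minimizing treatment bias adds: "Acupuncture will be performed by physicians of the department of the Interdisciplinary endoscopy center (IEZ"), so the acupuncturist is a physician of the same centre.
- **Who is kept uninformed.** The same section on measurement bias: "The physician performing the EGDE and the assistant nurse will not be informed about the allocation". No other staff are listed.
- **Who documents.** Also there: "A study nurse or physician will document and monitor the procedure in the endoscopy and recovery room". Nothing is said about whether this person is masked.
- **Examination quality.** Assessment of the primary endpoint: "The result will be documented in the CRF with tick boxes by the physician who performed the examination". That is the uninformed endoscopist.
- **Satisfaction.** Same section: "The patients are asked to rate their satisfaction with the examination after the completion of EGDE, prior to being told the results of their procedure". The rating is taken before the patient leaves the recovery room. Then: "The results will be documented in the CRF with tick boxes by a nurse or physician".
- **Willingness to repeat.** Under Secondary endpoints, this yes/no item is likewise recorded by a nurse or physician, without further condition.
- **Conversion to sedation.** Concomitant medication fixes satisfaction at 5/5 for converted patients, so no collected rating is used for them.

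**The concern.** The article assigns the two components of the composite differently. Examination quality goes to a named role that is masked. Satisfaction goes to an open category of staff that includes people who know, or could work out, the arm. For any patient who is not converted to sedation and has a 4/4 examination, the cut between 2 and 3 on the satisfaction scale alone decides success.

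Satisfaction is a subjective answer asked for by staff and entered by staff. A collector who knows the arm can prompt differently, or resolve a hesitant answer differently, in the two groups. Bias that differs by arm goes straight into the treatment comparison on the only primary endpoint, and no analysis can remove it afterwards.

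**Working it through.** **1. Who may collect the score, by role**

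| Role | Allocation status in the article | Permitted to record satisfaction? |
|---|---|---|
| Endoscopist | Not informed | Yes (a physician) |
| Assistant nurse | Not informed | Yes (a nurse) |
| Acupuncturist | Opens the envelope | Yes (a physician of the centre); not excluded anywhere |
| Study nurse or physician | Not stated | Yes; documents in the endoscopy and recovery rooms |

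The study nurse or physician need not see the envelope to learn the arm. Brief needle stimulation to produce the de qi sensation is described for the real arm (Intervention-group B) and not for the placebo arm (Intervention-group A). Someone who watches the needling could infer the group. The acupuncturist is also in contact with the patient up to the start of the procedure, since misplaced needles are "replaced by the physician who performed the acupuncture right before the examination". A further needle check follows the examination, but the article does not say who makes it.

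**2. The plan's own sample size** (Number of patients needed: 46% versus 61%, two-sided α = 0.05, power 80%)

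n per arm = [z₀.₉₇₅·√(2·p̄·(1−p̄)) + z₀.₈₀·√(p₁(1−p₁) + p₂(1−p₂))]² / (p₂−p₁)², with p̄ = 0.535

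= [1.3825 + 0.5869]² / 0.0225 = 172.4, rounded up to **173**, as stated. Power at 173 is 80.1%. For dropout, 346/0.98 = 353.06, which rounds up to the even total of **354**, as stated. The point below changes none of these figures.

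**3. Illustration of what a differential shift would do**

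Assumptions: no true effect; 46% success in the placebo arm; 173 per arm; biased collection raises the success rate in the real arm by b. The documents give no size for b.

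- SE₀ = √(2·p̄(1−p̄)/173), with p̄ = 0.46 + b/2
- SE₁ = √([0.46·0.54 + (0.46+b)(0.54−b)]/173)
- c = 1.96·SE₀
- Rejection probability = 1 − Φ((c−b)/SE₁) + Φ((−c−b)/SE₁)

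For b = 0.05: SE₀ = 0.0537, c = 0.1053, SE₁ = 0.0537, (c−b)/SE₁ = 1.031. The upper tail is 0.1513 and the lower tail 0.0019, total 0.153.

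| b (points) | Patients moved, of 173 | Rejection rate |
|---|---|---|
| 0 | 0 | 5.0% |
| 2 | 3.5 | 6.6% |
| 3 | 5.2 | 8.6% |
| 5 | 8.7 | 15.3% |
| 10 | 17.3 | 46.0% |

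**4. What b means among the patients who can be moved**

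Only unconverted patients with a 4/4 examination can change status. If they are a fraction q of the arm, an overall shift b needs a shift of b/q among them. The article does not give q. For the success rate to reach 0.46 + b, q must be at least 0.46 + b. The shift needed among these patients therefore lies between b (q = 1) and b/(0.46+b):

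- 3 points overall: 3.0 to 6.1 points (0.03/0.49)
- 5 points overall: 5.0 to 9.8 points (0.05/0.51)
- 10 points overall: 10.0 to 17.9 points (0.10/0.56)

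**The case against.** The strongest reply is that both raters are masked. The patient gives the satisfaction score and receives either real needles or a placebo needle system at the same points. The endoscopist, who gives the quality score, is not told the arm. The article nowhere says that the acupuncturist or another informed person collects satisfaction, and staff entry may mean no more than copying the patient's own answer. Who hands over a scale could also be left to the full protocol or to the manuals mentioned under Minimizing treatment bias.

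Much of this stands:

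- A reader might infer that the double-blind claim fails at outcome measurement, or that the endoscopist and assistant nurse are the only masked people. The documents support neither reading. The patient is masked, and collection by unmasked staff is permitted but not stated.
- A reader might assume that the study nurse sees the allocation, or that the acupuncturist makes the needle check after the examination. Neither is in the text.
- Politeness towards the person who placed the needles would act in both arms and would not by itself create a difference. Only a collector who behaves differently by arm would.
- The 3-, 5- and 10-point shifts are assumed. Ten points is two thirds of the planned 15-point effect and should not be read as likely.

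What does not stand is that this is only missing detail. The article does fix who records each component and which staff are uninformed. It restricts the recorder for one component and leaves the other open. A masked patient does not prevent an informed interviewer from influencing or misrecording the answer.

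**Conclusion.** The point holds as an unprotected step in outcome collection. The stated rules let staff who know or can infer the allocation elicit and record one of the two components of the sole primary endpoint, and also the willingness-to-repeat endpoint. They do not show that this happens, and no failure of blinding is demonstrated.

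The size is unknown. Under the assumptions in the working, the two-sided error rate would move from 5% to about 9%, 15% or 46% for differential shifts of 3, 5 or 10 points in the overall success rate. These figures are a sensitivity range, not an estimate. They show that about 5 to 9 altered patients in one arm would be enough to matter. The sample size and planned test are unaffected. The change is worth making because it costs very little and the bias could not be corrected later.

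**What to change.** In Assessment of the primary endpoint (satisfaction) and Secondary endpoints (willingness to repeat), state one of the following:

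- the patient completes both scales personally on a form page; or
- only staff who are uninformed of the allocation and were absent from the needling ask for and record the answers. The assistant nurse could do this if kept away while the needles are placed.

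In either case, add that the acupuncturist takes no part in collecting or recording these items.

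The cost is one extra form page and a short staff instruction, which can be given at the three-monthly training already planned. No extra staff are needed, and the 173 per group, the total of 354 and the analysis stay as they are.
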